### 2.4. Randomization

The 90 patients were allocated to the PA, MA, or UC groups in a 1:1:1 ratio by an independent statistician using computer-generated three- or six-block-size randomization. Each participant was selected via systematic sampling and was assigned an identification code enclosed in an opaque envelope. The assessors were blinded to the primary outcome and the Unified PD Rating Scale (UPDRS) II and III scores. In other words, the assessors collecting the data were blinded to the group allocation. The outcomes were evaluated by two assessors, one of whom was blinded and one who was not blinded. The enrollment of participants, allocation sequence, assignment to groups, and assessor blinding were the responsibility of the Clinical Trial Center of Kyung Hee University Hospital.

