### 2.8. Outcome Measures

The primary outcome measure was the King’s Parkinson’s Disease Pain Scale (KPPS) score at visits 1 and 18 to evaluate the effectiveness of PA for pain in PD. Pain in PD has been previously divided into three types—PD-directly related pain (related to disease onset), PD-indirectly related pain (aggravated by the disease), and PD-unrelated pain [17]. The KPPS has been validated for PD-directly related pain. As subjects with KPPS score >0 were enrolled in this study, the effectiveness of PA was limited to PD-directly related pain. The secondary outcome measures were the numerical rating scale (NRS) score for pain area and questionnaire survey (UPDRS II and III, Beck Depression Inventory II, Beck Anxiety Inventory, Euro-Quality of Life-5 Dimension, Pain Catastrophizing Scale, and PD Sleep Scale-2) results for related symptoms. To investigate the biological mechanisms underlying PD, exploratory outcome measures included MRI findings, molecular signatures in the blood, SD questionnaire survey, gait analysis, and facial expression analysis based on facial muscle response to emotional stimulation. The schedule for outcome measure assessments is presented in Table 2.

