### 2.11. Statistical Methods

#### 2.11.1. Sample Size Calculation

This study was a pilot clinical trial to determine the degree of symptomatic improvement that can be achieved with PA treatment in PD patients. Because of the lack of difference between the PA treatment group and the conventional treatment control group, the effect size was assumed based on similar previous studies, such as MA and bee venom acupuncture [34,35,36]. Accordingly, with a significance level of 5% and 80% power, the effect size was assumed to be 1.21. Considering a dropout rate, the calculated target sample size was 30 subjects per group.

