#### 2.11.2. Statistical Analysis

A complete set analysis was used to analyze the effectiveness of the intervention, and the per-protocol analysis was verified. For efficacy analysis, the mixed-effects model for repeated measures method was used, with each group and visit time as fixed factors and subjects as random factors. Student’s paired t-test or Wilcoxon signed rank test were used to compare factors before and after treatment within groups. All AEs, including SAEs, were classified by study group. All statistical analyses were performed using SAS^®^ version 9.4 (SAS Institute. Inc., Cary, NC, USA), and all *p*-values were two-sided. Statistical significance was set at a 5% level.

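### A random subject effect as the only within-patient dependence would, under correlation that decays with time, make the visit 1 to visit 18 KPPS test run at about 8% to 9.5% instead of 5%

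*Protocol article*

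**What the plan says.** Section 2.11.2 (Statistical Analysis) names a mixed-effects model for repeated measures for efficacy, "with each group and visit time as fixed factors and subjects as random factors". The subject effect is the only source of within-patient dependence mentioned. No residual covariance structure and no group-by-visit term is named. The p-"values were two-sided", and "Statistical significance was set at a 5% level". The paired tests in the same section compare before with after within a group, so the mixed model is the only between-group efficacy analysis described.

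Section 2.8 (Outcome Measures) sets the primary outcome as the "Pain Scale (KPPS) score at visits 1 and 18". Table 2 schedules KPPS at five visits: 1 (week −2 to −1), 3 (week 1), 10 (week 4), 18 (week 8) and 20 (week 12). It labels visit 3, not visit 1, as baseline. Allocation is "in a 1:1:1 ratio by an independent statistician", and "the calculated target sample size was 30 subjects per group". No standard deviation or between-visit correlation for KPPS is given.

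**The concern.** With no further covariance term, a random subject effect is compound symmetry: the same variance at each visit and the same correlation between every two visits. For a symptom score, correlation usually falls as visits lie further apart. Visits 1 and 18 are about 9 to 10 weeks apart and treatment starts between them, whereas other KPPS visits are only some 2.5 to 4 weeks apart. The fitted common correlation averages over all pairs, so it is too high for this distant pair. The variance of the change is then understated, the confidence interval is too narrow, and the test rejects more often than the stated two-sided 5%.

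**Working it through.** **Inputs from the article.** Two-sided 5%; three arms of 30; KPPS visits and weeks as in Table 2.

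**Inputs assumed.** Visit 1 at week −1.5; complete data; equal variances; correlation r = ρ^(gap in weeks / 4), with ρ from 0.5 to 0.9.

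**Formulas.** Let σ² be the variance at one visit, n the number per arm, r̄ the mean correlation over all pairs of modelled visits, and r the true correlation of the two visits compared. For the difference between two arms in mean change:

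- true variance = (2/n) · 2σ²(1 − r)
- variance reported by the random-subject model (balanced data) = (2/n) · 2σ²(1 − r̄)
- SE ratio (model/true) = √[(1 − r̄)/(1 − r)]
- actual error rate ≈ 2[1 − Φ(1.96 × ratio)]

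n and σ² cancel, so only the correlation pattern matters.

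**The plan's nominal 5%.** With constant correlation r̄ = r, the ratio is 1 and the rate is 5.0%. A simulation of 40,000 trials (3 × 30 patients, five visits, correlation 0.6) gives 4.9%. The nominal level therefore holds when the model is right.

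**Worked example, ρ = 0.7 per 4 weeks, five visits.** The ten gaps are 2.5, 5.5, 9.5, 13.5, 3, 7, 11, 4, 8 and 4 weeks. Their correlations are 0.800, 0.612, 0.429, 0.300, 0.765, 0.536, 0.375, 0.700, 0.490 and 0.700, so r̄ = 5.707/10 = 0.571. For visits 1 and 18, r = 0.429. The ratio is √(0.429/0.571) = 0.867, and 2[1 − Φ(1.699)] = 8.9%. Simulation also gives 8.9%. A contrast using its own variance, as an unstructured covariance would in balanced data, simulates at 5.0%.

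**Range, five visits modelled.**

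| ρ per 4 weeks | SE ratio, visit 1 to 18 | Error rate | SE ratio, visit 3 to 18 | Error rate |
|---|---|---|---|---|
| 0.5 | 0.889 | 8.1% | 0.953 | 6.2% |
| 0.6 | 0.877 | 8.6% | 0.956 | 6.1% |
| 0.7 | 0.867 | 8.9% | 0.962 | 5.9% |
| 0.8 | 0.858 | 9.3% | 0.968 | 5.8% |
| 0.9 | 0.852 | 9.5% | 0.976 | 5.6% |

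For visit 1 to 18 the model SE is thus 11% to 15% too small.

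**Sensitivity.**

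- *Visits 3, 10, 18 and 20 only, contrast visit 3 to 18.* About 6.6% to 7.3%, depending on whether correlation decays by week or by visit step.
- *Decay by visit step, visit 1 to 18.* 0.5 to 0.8 per step gives 8.1% to 10.0% (simulated 8.0% to 10.0%).
- *Unequal variances (0.7 per step).* Variance falling to 0.8 or rising to 1.2 of its first value leaves the rate at 9.4%.
- *Constant component added to the correlation.* With r = f + (1 − f)·decay, 1 − r is (1 − f)(1 − decay). The factor cancels and the rate does not change.
- *Independent visit-to-visit noise.* This dilutes the effect. With 30% noise at ρ = 0.7, the ratio is √[(0.3 + 0.7 × 0.429)/(0.3 + 0.7 × 0.571)] = √(0.600/0.700) = 0.926, or about 7%.
- *Only visits 1 and 18 modelled.* There is one pair, so r̄ = r and the rate is 5.0%.
- *Group main effect, or group difference at visit 18.* 5.0% with balanced data and equal variances.
- *Close pair, visit 3 to 10.* The error goes the other way: the SE is too large and the test runs at 0.7% to 3.1% (decay by step, 0.3 to 0.95).

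**The case against.** The strongest reply is that the article does not fix compound symmetry. It names a mixed model for repeated measures, a label often used for models with a flexible covariance. A random subject term can be combined with a structured residual covariance, and articles often describe such a model loosely in these words. An article may leave the residual covariance to the full protocol or analysis plan, so its absence alone is no fault. This stands: the sentence implies a common correlation only if nothing is added. What remains is that the one dependence term the article does state is, taken literally, the restrictive one.

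A second reply is that the inflated contrast has to be supplied by the reader. The section names no group-by-visit term, does not say which visits enter the model, and pairs with a primary outcome that could be modelled from visits 1 and 18 alone, where the problem vanishes. Table 2 also labels visit 3 as baseline, and from there the excess is small. This too stands and limits the scope. Still, comparing change between groups over the two visits named in section 2.8 is a natural reading of the primary outcome.

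A reader might infer that the plan's primary test has a false-positive rate of 9%. The document does not support that. It gives no correlation, and several readings of the text leave the rate at 5%. The trial also describes itself as a small pilot, which lowers the stakes.

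**Conclusion.** The point holds conditionally. Three conditions are needed: the random subject effect is the only covariance term, all five KPPS visits are modelled, and the between-group change from visit 1 to visit 18 is tested. Then, with correlation decaying at 0.5 to 0.9 per 4 weeks, equal variances and complete data, the nominal 5% test runs at about 8% to 9.5%. The excess is smaller from visit 3 and absent in the cases listed above. The correlations are assumptions; under decay the direction for the distant pair is stable but the size is not. It is a moderate point, worth correcting because the better specification is standard and cheap.

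**What to change.** Replace the random subject effect with a repeated visit effect within subject, with unstructured covariance and Kenward-Roger degrees of freedom. Pre-set the fallback if the model does not converge: heterogeneous Toeplitz, then compound symmetry with a sandwich variance. State the primary comparison as the group-by-visit contrast at visit 18 from one named baseline visit, and reconcile section 2.8 (visit 1) with Table 2 (visit 3). If the full protocol or analysis plan already says this, only the article's sentence needs correcting.

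The cost is about a sentence in the plan and a line of SAS code. An unstructured covariance has 5 × 6/2 = 15 parameters for five visits, or 4 × 5/2 = 10 for four, against 2 under compound symmetry. With 90 patients that is a small loss of degrees of freedom. If correlation is in fact constant, little is lost.

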### 2.12. Data Management and Monitoring

The investigator directly filled out electronic subject case report forms based on the survey questionnaire. The subjects were provided sufficient time to complete the questionnaires with the investigator’s assistance. All documents obtained in the clinical trial are to be preserved in the confidential archives at Kyung Hee University Hospital, Gangdong for 3 years. No information was shared without permission from the principal investigator. Regular monitoring of patient safety, investigation of AEs, and quality control of the data were performed by an independent monitoring committee unrelated to this study.

## 3. Discussion

This study investigated the clinical effectiveness and therapeutic mechanisms of PA as a non-pharmacological therapy in patients with PD pain. Pain in PD is a multifactorial phenotype [2] and can be categorized into several types [3,4]. To our knowledge, no clinical study has investigated the effect of PA on PD-directly related pain. Therefore, the primary outcome was the total KPPS score as an indicator of pain directly related to PD, as it measures the frequency, intensity, and location of each type of PD pain and rates the pain modifications associated with motor fluctuations in PD [1]. In a study on four factors of the KPPS, domains 1, 4, 6, and 7 measured skeletal/muscular pain caused by disorders in the peripheral nervous system, domain 2 measured the body’s internal pain, domain 3 assessed the pain associated with fluctuation states in PD, and domain 5 was the fourth factor [18]. By applying the domains of the KPPS to PD pain classification reported by Mylius et al. [4], domains 1, 3, 4, and 6 were included in the assessment of nociceptive pain. Domain 2 included nociplastic pain and domain 7 included neuropathic pain. Therefore, through a sub-analysis using the KPPS domains, PD pain mechanism-based classification, such as nociceptive pain, was possible. Additionally, the NRS score was a secondary outcome to evaluate pain intensity in each body part with pain.

In general, pain is a complex sensory and emotional experience that encompasses multiple somatic and affective domains. Negative affect, anxiety, and depression are commonly reported in various pain disorders [37,38,39], and patients with PD are also known to present with anxiety and depression in addition to pain [6,7]. Given the complexity of pain, we will evaluate both the sensory dimension (scales for pain intensity) and affective dimension (scales for depression, anxiety, and catastrophizing) of pain and their association in patients with PD.

Numerous neuroimaging studies on chronic pain have provided evidence on brain function and the networks supporting the neural mechanisms of somatic and affective pain processing. Several neuroimaging studies in patients with PD have demonstrated a correlation between aberrant functional connectivity of the dopaminergic pain pathway region and pain intensity [40], poorer pain network topology than that in healthy controls [16], and increased connectivity of the serotonergic brain region to pain-related brain regions [41]. A previous study revealed that persistent pain in PD is associated with gray matter changes and functional brain networks [42]. However, the neural mechanism underlying the association between the somatic and affective domains of pain in PD remains unclear. In our study, we adopted multimodal brain imaging techniques and multidimensional pain evaluations. Based on previous studies, we investigated changes in pain-related symptoms and the structural and functional differences between patients with PD and healthy controls. Furthermore, the association between the central mechanism of pain processing will be investigated using brain estimates and multidimensional pain scales.

One limitation of this study is the fact that it was a small pilot clinical trial. However, this study could potentially be a basis for future large-scale clinical studies, thereby addressing the lack of evidence on the effectiveness of PA in the treatment of pain in PD. Another limitation is that this study could set the conditions of the interventions; the control group was administered UC instead of a placebo because of the pragmatic RCT design, and the efficacy of PA as an intervention could not be confirmed. However, this pragmatic RCT reflecting standard therapy and UC may provide results that can directly inform real-world clinical practice [43]. In addition, the usefulness of sham acupuncture as a placebo control method remains debatable because its beneficial effects cannot be excluded [44]. Moreover, masking is not possible for sham acupuncture, given the nature of the intervention [43]. Consequently, the control group in this trial received MA or UC. Further research will be required to validate our findings.

## 4. Ethics and Dissemination

The IRB of Kyung Hee University Korean Medicine Hospital, Gangdong approved the protocol of this clinical trial and accepted responsibility for supervising all aspects of the study (approval number: KHNMCOH 2022-02-005-001). Study participation was voluntary, and a signed informed consent form was obtained from all participants. All participants and their families were informed of the potential risks and benefits of treatment. The study protocol (version 1.2, 7 March 2022) was registered with the Clinical Research Information Service, the 11th member to have joined the World Health Organization International Clinical Trials Registry Platform as the primary registry representing the Republic of Korea (registration number: KCT0007254). In cases of significant protocol changes, the research coordinator requested additional approval from the IRB and trial registries. The results of this study were disseminated through publications in peer-reviewed journals.

## 5. Conclusions

To the best of our knowledge, this study was the first clinical trial on the clinical effectiveness of PA, which is commonly used in South Korea to treat pain in PD, and to include neuroimaging changes and molecular signature indicators. We expect to demonstrate improvements in pain and related symptoms, and changes in the levels of molecular markers. Our data provide insights into the mechanisms underlying the therapeutic effects of PA and helps to identify potential complementary therapies for pain in PD.

## Figures and Tables

**Figure 1 ijerph-20-01776-f001:**
[figure not shown]
Subject selection flowchart. PA, pharmacopuncture; MA, manual acupuncture; UC, usual care; MRI, magnetic resonance imaging; HC, healthy control.

**Table 1 ijerph-20-01776-t001:** Patient eligibility criteria.

Inclusion Criteria
Adult patients (age ≥ 19 years)
Diagnosis of idiopathic PD based on the UK Parkinson’s Disease Society Brain Bank criteria
Hoehn and Yahr Scale stage 1–4
King’s Parkinson’s Disease Pain Scale score > 0
A stable dose of conventional treatment for at least 4 weeks prior to enrollment
Terminated PA or MA treatment 4 weeks before enrollment
Provide voluntary written informed consent to participate in this clinical study
**Exclusion criteria**
Parkinson-plus syndromes (i.e., multisystem atrophy, progressive supranuclear palsy, corticobasal degeneration, and dementia with Lewy bodies)
Pain unrelated to PD (e.g., postoperative pain)
History of neuropsychiatric disorder unrelated to PD
Moderate or higher cognitive impairment that will interfere with the evaluation of treatment effects
Severe acute cardiovascular disease (i.e., heart failure, myocardial infarction, stroke, and hypertension)
Serious conditions (i.e., anemia, active pulmonary tuberculosis, thyroid disease, and other infectious and systemic diseases)
Active cancer
Uncontrolled hypertension (systolic blood pressure > 160 mmHg or diastolic blood pressure > 100 mmHg)
History of hypersensitivity reactions to PA
Indications for PA treatment being inappropriate or unsafe (i.e., hemorrhagic disease, patients with severe diabetes who have a higher risk of infection)
History of taking oral adrenal corticosteroids (steroids), immunosuppressants, or antipsychotic drugs or other drugs that may affect clinical trial results within the last 4 weeks
Inability to undergo MRI
Pregnant or lactating women or current contraceptive use among women of pregnant potential who are likely to become pregnant (except for women who have undergone sterilization)
History of drug or alcohol abuse
Unstable medical condition as determined by the research clinician; A patient who shows clinically significant diseases and disorders in physical or clinical examination or is receiving active treatment thereof
Participation in another clinical trial within the last 4 weeks
History of vaccination within 4 weeks or plans to be vaccinated during the clinical trial period
Inappropriate for enrollment due to other reasons as determined by the investigator

PD, Parkinson’s disease; PA, pharmacopuncture; MA, manual acupuncture; MRI, magnetic resonance imaging.

**Table 2 ijerph-20-01776-t002:** Schedule of enrollment, clinical outcomes, and safety assessment.

		Screening	MRI	Treatment			MRI	Follow-Up
Week		−2 to −1	−1 to −0	1	4	8	8 to 9	12
Visit No.		1	2	3 (Baseline)	10	18	19	20
Provide informed consent		O						
Identification of inclusion and exclusion criteria		O						
Demographics		O						
Medical and disease history		O						
Vital signs		O	O	O (every visit)	O (every visit)	O	O	O
Clinical laboratory examination		O				O		
Identification of eligibility criteria for MRI measurement		O						
Randomization		O						
Outcome measures	KPPS	O		O	O	O		O
	NRS			O	O	O		O
	UPDRS II, III			O	O	O		O
	Pain catastrophizing score			O		O		
	EQ-5D			O		O		
	PDSS-2			O		O		
	Facial expression analysis			O		O		
	Syndrome differentiation		O				O	
	BDI II		O				O	
	BAI		O				O	
	Gait analysis			O		O		O
MRI measurement			O				O	
Blood collection for molecular analysis		O				O		
PA or MA or UC				O (every visit)	O (every visit)	O		
Treatment compliance						O		
Identification of concomitant drug change		O	O	O (every visit)	O (every visit)	O	O	O
Identification of adverse reaction(s)					O (every visit)	O	O	O

MRI, magnetic resonance imaging; KPPS, King’s Parkinson’s Disease Pain Scale; NRS, numerical rating scale; UPDRS, Unified Parkinson’s Disease Rating Scale; EQ-5D, Euro-Quality of Life-5 Dimension; PDSS, Parkinson’s Disease Sleep Scale; BDI, Beck Depression Inventory; BAI, Beck Anxiety Inventory; PA, pharmacopuncture; MA, manual acupuncture; UC, usual care

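### Table 1's pregnancy exclusion appears to have lost a negation: as printed it bars contraceptive users of child-bearing potential and does not bar non-users

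*Protocol article*

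**What the plan says.** Table 1 of the protocol article has an inclusion list and a list headed "Exclusion criteria". One item in the second list begins "Pregnant or lactating women or current contraceptive use among women of pregnant potential". The contraception clause in full is "current contraceptive use among women of pregnant potential who are likely to become pregnant (except for women who have undergone sterilization", after which the bracket closes. It contains no *not*, *without* or *lack of*.

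Three other places bear on how the line operates:

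- **Section 2.3 (Participant Recruitment)** makes Table 1 the standard that participants had to meet, and Table 2 schedules the check of inclusion and exclusion criteria at visit 1.
- **The age criterion in Table 1** is "Adult patients (age ≥ 19 years" and has no upper limit, so women of child-bearing potential can be screened.
- **The last exclusion item** is a general one: "Inappropriate for enrollment due to other reasons as determined by the investigator". It does not mention contraception.

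**The concern.** A criterion in an exclusion list bars whoever meets it. Here the condition is use of contraception, when the evident purpose is to keep out women who might conceive during treatment. Followed as printed, the line refuses women who take the precaution and leaves those who do not outside its reach.

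What is at stake is participant protection, not the statistics. In the pharmacopuncture arm a nine-ingredient extract is injected at acupoints (Section 2.6) twice a week for 8 weeks (Section 2.5), which is 2 × 8 = 16 sessions. The article gives no reproductive-safety information on the extract, so no size of harm can be stated. Section 3 also presents this pilot as groundwork for larger trials, so a reversed criterion could be copied into a later protocol.

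**Working it through.** No arithmetic in the plan bears on this point. The check is a reading of the rule, case by case, followed by a search for anything that corrects it.

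**Step 1. Apply the printed line to each reproductive status it covers.** The intended column is inferred from the line's own qualifiers (step 2).

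| Case | As printed | Evident intent | Result |
|---|---|---|---|
| Pregnant or lactating | Excluded | Excluded | Agrees |
| Child-bearing potential, using contraception | Excluded | Eligible | Reversed |
| Child-bearing potential, no contraception | Not excluded | Excluded | Reversed |
| Sterilised | Eligible | Eligible | Agrees |

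Reversed: 2 of 4. This counts categories, not patients.

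**Step 2. Is it an error or a deliberate rule?** Two features of the line fit only a rule against the absence of contraception. First, it describes the women concerned as likely to become pregnant, which suits women without protection. Second, it exempts sterilised women. That exemption makes sense if the rule demands contraception, which they do not need, and serves no clear purpose if the rule forbids it. The alternative is a deliberate ban on contraceptive drugs as interfering medication. That fits poorly: interfering drugs have their own exclusion item with a 4-week window, this clause is not limited to drugs, and it shares an item with pregnancy and lactation.

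**Step 3. Does the reading depend on how the likelihood qualifier is taken?** If it merely restates fertility, the table above stands. If it is a real restriction, a woman on effective contraception arguably falls outside the clause, and the second row is muddled, not cleanly reversed. The third row is the same under both readings: a woman who uses no contraception is not a current user, so the line does not reach her.

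**Step 4. Is it corrected elsewhere?** No other part of the article mentions pregnancy or contraception, and Table 2 has no separate pregnancy-test row. Three other provisions narrow the gap without correcting the line:

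- Pregnant and lactating women remain excluded by the first part of the same item.
- The item on patients for whom pharmacopuncture is unsuitable or unsafe gives only haemorrhagic disease and severe diabetes as examples.
- The investigator's general discretion can keep out a non-user case by case. It cannot admit a contraceptive user, because discretion to exclude does not waive a printed exclusion.

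**The case against.** The strongest reply accepts that the wording is defective but calls it a copy-editing matter. The qualifiers reveal the intent, so a screening clinician would probably not apply the line backwards. The article condenses an approved protocol, version 1.2 of 7 March 2022 (Section 4), and nothing shows that screening was done from the journal table. Investigator discretion means that entry for a non-user is not automatic. The injection concern applies to one arm of three. Few women of child-bearing potential are likely in a Parkinson's disease population.

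Most of this stands as a limit on the consequences. Only the error in the article's Table 1 is established. Whether any woman was wrongly refused or admitted depends on a document that is not shown, and no operational harm is claimed. The expectation that few women are affected is reasonable, but it is an assumption, since the article gives no figure.

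The reply does not remove the point. The article does not leave this criterion to the full protocol: it states it, and states it wrongly. Section 2.3 names the same table as the test for entry. A rule that works only if the reader silently reverses it should not stand in an eligibility list, however few patients it touches. Nor does the one-arm argument help at screening, because all patients are screened against one list and any of them may be allocated to pharmacopuncture.

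**Conclusion.** The concern holds. As printed, the contraception clause in Table 1 fails to exclude women of child-bearing potential who use no contraception, under either reading of its qualifier. Under the natural reading it also excludes those who do use it. It is most likely an unintended wording error, not a design decision.

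Two of the four reproductive-status cases are reversed. The patient count cannot be derived and is probably small. Sample size, power and the primary analysis are unaffected. The conclusion rests on the printed text and on an intent inferred from the line itself; it says nothing about the wording of version 1.2 or about what happened at screening. The wording should be corrected, but it does not threaten the trial's conclusions.

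**What to change.** Reword the item along these lines: *Pregnant or lactating women, or women of child-bearing potential not using adequate contraception during the trial (except women who have undergone sterilisation).* The essential change is the restored negation. The words *adequate* and *during the trial* are customary but do not appear in the printed line, so they should be kept only if they agree with the approved protocol.

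Then compare the line with protocol version 1.2:

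- **If version 1.2 is worded correctly**, correct the published table and do nothing more.
- **If version 1.2 has the printed wording**, amend it through the ethics board and check the screening log for women wrongly refused or enrolled.

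The cost is a one-line correction and one document comparison. The amendment and log check arise only in the second case.
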